### Objectives and hypothesis

The primary objective of the trial is to evaluate the effects of a 4-day hospital-based intervention for primary caregivers of children with SAM on child development and nutritional status after 6 months.

The secondary objective is to understand the effects of this programme on knowledge, attitudes, and practices, as well as mental health status of primary caregivers.

The hypothesis is that the intervention programme for primary caregivers will improve developmental and nutritional outcomes in children hospitalized with SAM.

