### Primary outcome

The primary outcome is child development 6 months after discharge (*t*
_*6*_). Child development will be assessed with the MDAT. The MDAT has been evaluated in 1426 healthy Malawian children as well as children with neurodisability (*n* = 80) or with severe wasting (*n* = 120) [23]. In this evaluation, sensitivity was 97%, and 18% of healthy children failed, translating to specificity of 82% [23]. These results show that the MDAT is an appropriate tool for assessing child development in Malawi.

The MDAT will be used at discharge (*t*
_*5*_) and 6 months later (*t*
_*6*_) to examine development in four domains: gross motor, fine motor, language, and social development [23]. Children will be given a pass or fail depending on their ability to complete increasingly advanced items on the MDAT [23]. The sum of passed items can be calculated and translated to age-specific *z* scores based on healthy Malawian children as reference standards [23].

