### Secondary outcomes

Data will be collected at three time points: at enrollment (–*t*
_*1*_), discharge from hospital (*t*
_*5*_), and 6 months after discharge (*t*
_*6*_). All outcomes and measures are described in Table 1.

**Table 1 Tab1:** Primary, secondary, and implementation outcomes and measures

Outcomes	Measures
Primary outcome	
Child development: gross motor, fine motor, language, and social development (*t* _*6*_)	Malawi Developmental Assessment Tool (MDAT)
Secondary outcomes (child)	
Nutritional status (*t* _*6*_)	Mid-upper arm circumference (MUAC) Weight-for-length or -height *z* scores (WLZ or WHZ) Presence of bilateral pitting oedema Height-for-age *z* scores (HAZ)
Dietary intake (*t* _*6*_)	24-h dietary recall
Readmission to hospital (*t* _*5*_–*t* _*6*_)	Record of readmission to hospital for severe acute malnutrition (SAM)
Mortality (*–t* _*1*_ to *t* _*5*_ or *t* _*5*_–*t* _*6*_)	Death of child confirmed
Secondary outcomes (primary caregiver and household)	
Mental health status (*t* _*6*_)	Self-Reporting Questionnaire-20 (SRQ-20)
Nutritional status (*t* _*6*_)	Mid-upper arm circumference (MUAC) Body mass index (BMI)
Knowledge, attitudes, and practices (*t* _*6*_)	Questionnaire about hygiene and sanitation, nutrition and feeding, and malnutrition 24-h dietary recall of child
Stimulus and support for children in the household (*t* _*6*_)	Home Observation of the Measurement of the Environment (HOME) Inventory
Implementation outcomes	
Participant engagement (*t* _*1*_)	Number of enrolled participants who attend day 1 of the Kusamala Program
Participant adherence (*t* _*1*_–*t* _*4*_)	Number of enrolled participants who attend all 4 days of the Kusamala Program
Fidelity of the intervention programme	Assessment form of Kusamala Program delivery
Participant knowledge and attitudes of intervention content (*t* _*5*_)	Questionnaire about hygiene and sanitation, nutrition and feeding, and malnutrition

Important child outcomes are the nutritional status assessed by anthropometry (i.e. MUAC, WLZ or WHZ, oedema, and height-for-age *z* scores) and dietary intake based on a locally adapted 24-h dietary recall which will be performed only at follow-up (*t*
_*6*_) [32, 33]. Readmission to hospital and mortality at any time point are other secondary outcomes of interest. Child co-variates that will be considered include sex, age, and HIV status.

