### Sample size calculation

The sample size estimate is based on cross-sectional study data of development of children with SAM at discharge from the NRU using the MDAT [38]. Results from this study showed that, based on MDAT *z* scores, the variance for gross motor was 1.9 SD, for fine motor was 1.2 SD, and for language was 1.7 SD [38]. Therefore, the composite variance for those domains was 1.6 SD. This was used to calculate the sample size using α = 0.05 and 80% power, an estimated intracluster correlation coefficient of 0.001, and with an expected effect size of 0.5 using Cohen’s *d* [39, 40]. With this approach, the initial estimate of the sample size for the primary outcome is a minimum of 160 primary caregiver-child pairs per arm (*n* = 320). As discussed previously, an internal pilot study will be conducted to determine the variance of the primary outcome in the first 15 children in each study group at 6 months post-discharge from hospital which will be used to recalculate the sample size [25].

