**Fig. 2 Fig2:**
[figure not shown]
Modified version of the CONSORT 2010 flow diagram

Data will be analysed using the statistical software Stata 14, R v3.2.5, and WHO Anthro v3.2.2 for anthropometric *z*-score calculations [43–45]. Missing data will be accounted for depending on the nature of drop-outs and loss to follow-up.

Descriptive statistics will be performed to summarize baseline characteristics of participants in both the intervention and comparison groups. More specifically, means and SD will be calculated for continuous variables such as the age of children, whereas the number of participants and percentages will be calculated for categorical variables such as the presence of oedema.

MDAT *z* scores standardized by age and based on a reference population of Malawian children will be calculated [23]. *Z* scores of each domain will be analysed separately to understand if the intervention influences certain domains more than others and a composite score of overall child development will be calculated if statistically appropriate. Upon completion of data collection for the internal pilot study, the variance of the primary outcome, child development using the MDAT, will be determined. The variance will be used to recalculate the sample size for the full trial [25, 26].

To determine the effect of the intervention on the primary outcome measures and continuous secondary outcomes, analysis of co-variance (ANCOVA) will be conducted to determine if there are differences between the intervention groups and the comparison groups while allowing for adjustment of co-variates in the analysis [46].

Multiple logistical regression will be performed to determine whether the intervention influenced binary outcomes such as the presence or absence of oedema. Subgroup analyses will be performed with participant age categories (i.e. infants and older children) and types of SAM (i.e. marasmus and kwashiorkor), and neurodisability, since children with neurodisability such as cerebral palsy are included in this study.

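### No single MDAT score decides the primary question, and the sample size rests on a three-domain SD that belongs to no analysis the plan commits to

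*Protocol article*

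**What the plan says.** Under Primary outcome the protocol article states that "The primary outcome is child development 6 months after discharge". The MDAT is to be used "to examine development in four domains: gross motor, fine motor, language, and social development". Table 1 gives the primary outcome as "Child development: gross motor, fine motor, language, and social development", all on one line, with no domain ranked above another.

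Under Statistical analysis, the plan for the individual domains is that "scores of each domain will be analysed separately to understand if the intervention influences certain domains more than others". For an overall score, the same sentence commits only to this: "a composite score of overall child development will be calculated if statistically appropriate". ANCOVA is then applied "To determine the effect of the intervention on the primary outcome measures and continuous secondary outcomes", with measures in the plural.

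The Sample size calculation section gives figures of 1.9, 1.2 and 1.7 SD for gross motor, fine motor and language, and says that "the composite variance for those domains was 1.6 SD". With α = 0.05, 80% power, an intracluster correlation of 0.001 and an effect of 0.5, it arrives at 160 pairs per arm. That number is an initial estimate, to be recalculated from the variance of the primary outcome in the internal pilot.

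**The concern.** The only analyses to which the plan is committed are four domain analyses. The one quantity that could serve as a single primary endpoint, the composite, exists only if an unspecified condition is met. The article does not say what the condition is, who judges it, when, or how the composite would be formed. If the four domains disagree, nothing in the plan says whether the primary hypothesis has been supported.

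The sample size has the same gap. It is worked out for a composite of three domains, while the primary outcome has four and the composite may never be calculated. The stated 80% power then describes no analysis that is certain to be done. The pilot re-estimation inherits the problem: the variance of the primary outcome could mean any of four domain variances or that of a composite, and these lead to very different sample sizes.

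**Working it through.** **Inputs.** From Sample size calculation: SDs 1.9 (gross motor), 1.2 (fine motor) and 1.7 (language); composite 1.6; effect 0.5; α = 0.05; power 80%; intracluster correlation 0.001; 160 per arm. From Trial overview and design: an average of four pairs per weekly group. Assumed: two-sided testing (sidedness is not stated), no covariate adjustment, and the between-domain correlations, which the article does not give. No SD is given for the social domain.

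**Reproducing the plan's figure.**
- n per arm = 2 × (SD × (1.960 + 0.842) / difference)² = 2 × (1.6 × 2.802 / 0.5)² = 160.7.
- Design effect = 1 + (4 − 1) × 0.001 = 1.003, giving 161.2. This agrees with the stated 160.
- It agrees only if 0.5 is a difference in z-score units. As a standardised effect that is 0.5 / 1.6 = 0.31; a true standardised effect of 0.5 would need 63 per arm.

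**Where 1.6 comes from.** (1.9 + 1.2 + 1.7) / 3 = 1.60. The root mean square, √((3.61 + 1.44 + 2.89) / 3) = 1.63, also rounds to 1.6. The article shows no formula, so either is possible. Both are averages of the three domain SDs, and neither includes social.

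**Power for each domain at 160 per arm.** Two-sample t test, effective n = 160 / 1.003 = 159.5 per arm, difference 0.5. The last column is n for 80% power by the formula above, times 1.003, rounded up.

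| Score | SD | Power | n per arm for 80% |
|---|---|---|---|
| Gross motor | 1.9 | 64.9% | 228 |
| Language | 1.7 | 74.5% | 183 |
| Fine motor | 1.2 | 96.0% | 91 |
| Social | not given | not computable | not computable |

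**Power for a mean of the three domains.** SD of the mean = √(Σ SDᵢ² + 2r Σ SDᵢSDⱼ) / 3, with Σ SDᵢ² = 7.94 and Σ SDᵢSDⱼ = 2.28 + 3.23 + 2.04 = 7.55.
- r = 0.5: √(7.94 + 7.55) / 3 = 1.31; power about 92%.
- r = 0.7: √(7.94 + 10.57) / 3 = 1.43; power about 87%.
- r = 1: √(7.94 + 15.10) / 3 = 1.60; power about 80%.

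So 1.6 is the SD of a mean score only if the three domains correlate perfectly. At any lower correlation it is too large for that score, and the sample size is generous.

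**False-positive chance, if any one of four domains at 0.05 counted as success.** Under independence, 1 − 0.95⁴ = 18.5%. By simulation with a common correlation, about 16% at 0.5 and 13% at 0.7. Adding an equally weighted composite of the same four domains gives about 20% at correlation 0, 16% at 0.5 and 13% at 0.7.

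**The case against.** Several points on the other side stand.

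- The purpose given for the separate domain analyses reads as explanatory, and α = 0.05 appears only in the sample size section. A reader might infer that each domain is tested at 0.05 and that one significant domain would be claimed as success. The article says neither, so the error rates above are conditional on that reading.
- A reader might also infer that the composite would be chosen after seeing the results. The timing is not stated, and the analysis is to be blinded with a dummy-coded group variable. The wording leaves room for selection but does not plan it.
- Treating the composite as a fifth independent test would give 1 − 0.95⁵ = 22.6%. That is wrong, because the composite is built from the four domains. It adds at most about 2 percentage points.
- The SD of 1.6 is conservative for fine motor and for a mean score. The 160 is expressly provisional, and covariate adjustment in the ANCOVA could raise power above the unadjusted figures.
- The primary objective speaks of effects "on child development and nutritional status after 6 months", which might suggest a second primary endpoint. The abstract, the design section, the Primary outcome section and Table 1 all make the MDAT alone primary, so this is loose wording.
- Multiplicity detail may properly sit in a statistical analysis plan that is not shown.

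None of this supplies a decisive score. If the domain analyses are explanatory, nothing unconditional is left as primary. The difficulty is what the article states, a composite subject to an undefined condition, and not detail it has left out.

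**Conclusion.** The point holds as a mismatch between endpoint, analysis and sample size. As written, no single MDAT score answers the primary question, and the 80% power attaches to no analysis the plan is committed to. For a 0.5 z difference at 160 per arm, unadjusted power runs from about 65% to 96% across the three domains with a stated SD, and is unknown for social. A three-domain mean would have about 87% to 92% at assumed correlations of 0.7 and 0.5. To conclude that the trial is simply underpowered would go further than these figures allow.

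The pilot re-estimation does not settle the matter. Depending on which variance it uses, 80% power needs anything from 91 per arm (fine motor) to 228 (gross motor), and the protocol does not say which applies.

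The false-positive chance of 18.5% under independence, or about 13% to 16% at correlations of 0.7 and 0.5, rests on an any-domain rule that the text does not contain. It shows what the open wording would allow, not what the trial intends.

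**What to change.** Before anyone sees unblinded outcome data:

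1. Name one primary MDAT score at 6 months and give its formula. The mean of the four domain z scores is one option; another overall score would serve if fully defined.
2. Test that score once at two-sided 0.05, and remove the condition attached to the composite.
3. Make the four domains secondary, with a stated multiplicity adjustment such as Holm.
4. Restate the power for that score using its own SD, and specify that the internal pilot estimates the variance of that same score.

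As a minor wording change, bring the primary objective into line with Table 1, where nutritional status is secondary.

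The cost is a protocol amendment, for which the article already describes a route through both ethics boards. The real price is that claims about a single domain face a stricter threshold. The recalculated sample size may move in either direction, depending on the SD of the chosen score.

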**Methods:**

A cluster-randomized controlled trial at the Queen Elizabeth Central Hospital in Blantyre, Malawi will be conducted to evaluate the effectiveness of a 4-day hospital-based intervention programme directed at primary caregivers. This programme, titled the Kusamala Program, aims to improve developmental and nutritional outcomes in children with SAM. Up to six primary caregivers and their children will be enrolled to groups each week, which will be randomly allocated to intervention or comparison arms. The intervention package consists of interactive counselling on three modules: 1) nutrition and feeding; 2) water, sanitation, and hygiene (WASH); and 3) psychosocial stimulation. Data collection will be performed at enrolment, at discharge from hospital, and at 6 months following discharge. The primary outcome is child development assessed with the Malawi Developmental Assessment Tool (MDAT), a validated measure of gross and fine motor, language, and social development.

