### Trial overview and design

This study will evaluate a comprehensive structured intervention package for primary caregivers of children aged 6 to 59 months hospitalized with SAM. It will be a pragmatic trial aimed at replicating how this type of intervention could be delivered in a real nutrition rehabilitation unit (NRU) setting and its effectiveness in this setting [22]. The primary outcome is child development, which will be assessed using the Malawi Developmental Assessment Tool (MDAT), a locally adapted and validated tool for evaluating multiple domains of child development (i.e. gross motor, fine motor, language, and social domains) [23].

The design of the study is a cluster-randomized controlled trial (superiority design) that will be conducted at the Moyo NRU of the Queen Elizabeth Central Hospital in Blantyre, Malawi (NCT03072433). A cluster-randomized controlled trial design was selected because the intervention is most feasible if delivered to groups of primary caregivers rather than individual caregivers. This design will also prevent temporal overlap between the two study arms: 1) an intervention arm of primary caregivers and children with SAM participating in an intervention programme; and 2) the comparison arm of primary caregivers and children with SAM receiving standard care. All other clinical and nutritional aspects of care will be equivalent; children will be treated per hospital protocol and WHO guidelines [24]. One day of each week will be used to recruit and enrol an estimated average of four primary caregiver-child pairs. Once formed, the group will be randomly assigned to either the intervention or comparison arm. Recruitment and enrolment will not overlap with the delivery of intervention sessions, although it is possible that children from different groups will be in the NRU at the same time depending on the duration of their in-patient treatment.

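### Weekly groups are randomised and the sample size carries an ICC, but the named analyses (ANCOVA and logistic regression) give no term or variance correction for the group

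*Protocol article*

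**What the plan says.** **Unit of randomisation.** Trial overview and design describes a cluster-randomised superiority trial. One day a week is used to enrol "an estimated average of four primary caregiver-child pairs", and then: "Once formed, the group will be randomly assigned to either the intervention or comparison arm". The Abstract gives the ceiling on group size: "Up to six primary caregivers and their children will be enrolled to groups each week".

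**Sample size.** The Sample size calculation section recognises the clustering. It uses "an estimated intracluster correlation coefficient of 0.001", with α = 0.05, 80% power, an effect of 0.5 and an SD of 1.6, and arrives at 160 pairs per arm (320 in total).

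**Analysis.** The Statistical analysis section names the models. For child development, and for secondary outcomes on a continuous scale, the text reads: "analysis of co-variance (ANCOVA) will be conducted to determine if there are differences between the intervention groups and the comparison groups", with adjustment for covariates. For the rest, "Multiple logistical regression will be performed to determine whether the intervention influenced binary outcomes". The covariates listed under Secondary outcomes are characteristics of the child, caregiver and household. The weekly group is not among them. The article nowhere mentions a group random effect, GEE, cluster-robust errors or a group-level analysis.

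**Internal pilot.** The quantity to be re-estimated for the sample size is the variance of the MDAT score. The ICC is not mentioned.

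**The concern.** When groups are randomised, the treatment effect has to be judged against variation between groups. ANCOVA and logistic regression, as ordinarily understood, judge it against variation between individual children and count every child as an independent observation. If children in the same weekly group resemble each other at all, the standard error is too small and the nominal 5% test rejects too often. This would affect the primary comparison and every secondary comparison analysed in the same way.

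The article gives reasons why groups might differ. Caregivers in a group are enrolled on the same day, counselled together and take part in supervised play together. Five nurses were trained to deliver the programme, and fidelity is to be assessed in a fifth of sessions, so variation in delivery is treated as possible. The ICC of 0.001 is described only as an estimate. An analysis that ignores groups depends on that value being about right, whereas one that includes them does not.

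**Working it through.** **Inputs from the article.** Average group size m = 4, planning ICC ρ = 0.001 and 160 pairs per arm. About 80 groups follow from 320/4 = 80, which agrees with the roughly 80 weekly cycles under Data collection and management. SD is 1.6 (the mean of 1.9, 1.2 and 1.7), difference 0.5, α = 0.05 and power 80%.

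**Assumptions.** The tests are two-sided, and the groups all have four pairs. ICCs above 0.001 are illustrative, because the article gives none.

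**1. The plan's own figure.** Reading 0.5 as raw z-score units:

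n per arm = 2 × [1.6 × (1.960 + 0.842) / 0.5]² = 160.7

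The design effect is DE = 1 + (m − 1)ρ = 1 + 3 × 0.001 = 1.003, and 160.7 × 1.003 = 161.2, which rounds up to 162. This reproduces the stated 160 to within 2%. The ICC adds less than one pair per arm. (A true standardised effect of 0.5 would need only 63 per arm. That labelling problem is separate from this point.)

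**2. Type I error of an individual-level test when both arms are clustered.** The reported standard error is 1/√DE of the correct one, and the actual type I error is 2 × [1 − Φ(1.96/√DE)].

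| ICC | DE | Reported SE ÷ correct SE | 1.96/√DE | Type I error |
|---|---|---|---|---|
| 0.001 (planning) | 1.003 | 0.9985 | 1.957 | 5.03% |
| 0.01 (assumed) | 1.03 | 0.985 | 1.931 | 5.35% |
| 0.05 (assumed) | 1.15 | 0.933 | 1.828 | 6.8% |
| 0.10 (assumed) | 1.30 | 0.877 | 1.719 | 8.6% |

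**3. The same when only the intervention arm is clustered.** If the correlation comes only from the shared sessions, the comparison arm has a design effect of 1. With equal arms, the variance of the difference is inflated by (DE + 1)/2.

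- ICC 0.05: (1.15 + 1)/2 = 1.075; 1.96/√1.075 = 1.890; type I error 5.9%.
- ICC 0.10: (1.30 + 1)/2 = 1.15; 1.96/√1.15 = 1.828; type I error 6.8%.

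**4. Simulation check.** There were 40 groups of four per arm, both arms clustered, with 20,000 runs (Monte Carlo standard error about 0.15 percentage points).

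| ICC | Individual-level t-test | t-test on group means |
|---|---|---|
| 0.001 | 4.8% | 4.8% |
| 0.01 | 5.1% | 5.0% |
| 0.05 | 6.6% | 4.9% |
| 0.10 | 8.8% | 5.1% |

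At the two small ICCs the excess cannot be told from simulation noise. At 0.05 and 0.10 the formula is confirmed, and the group-level test holds its level.

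**5. Power of a correct analysis at 160 per arm.** With both arms clustered, power is 79.7% at ICC 0.001, 74% at 0.05 and 69% at 0.10. With only the intervention arm clustered, it is 77% at 0.05 and 74% at 0.10.

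**The case against.** **The article is condensed and a statistical analysis plan may exist.** How the group enters the model, or which variance estimator is used, is the kind of detail such a plan supplies. ANCOVA can also be run with a random group factor or on group summaries. A reader might infer that the protocol declares children independent, but it does not. That follows only from the usual meaning of the methods named. What remains is that the article does not defer the choice of model. It names one for the primary outcome and one for binary outcomes, and describes covariate adjustment as the only addition. Followed as written, this leaves out the unit of randomisation.

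**The harm is negligible on the protocol's own figures.** This is correct and sets the scale of the point. Material inflation needs an ICC 50 to 100 times the planning value, and no part of the article supports such a value. Some features suggest a small ICC: a single site, families living far apart, and outcomes measured six months later, mostly at separate home visits. Against that, the planning value is only an estimate, and a valid analysis should not depend on it.

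**Some stronger arguments should not be used.**
- A reader might suppose that one nurse runs each group. The article says only that nurses of the unit lead the sessions and that five were trained.
- Error rates worked out for groups of six treat the maximum as the size of every group, whereas the article expects an average of four.
- The pilot's silence on the ICC is a weak complaint. At least 30 pairs is about eight groups, too few to estimate an ICC usefully, and nothing prevents its being reported at the end.

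**Conclusion.** The point holds as a mismatch between the design and the named analysis. Groups are randomised and the sample size acknowledges it, but the models as named do not. The direction of error is certain for any positive ICC if they are run in their ordinary form.

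The size depends on an ICC that the article does not establish. At 0.001 the standard error is 0.15% too small, which has no practical consequence. Type I error reaches roughly 6% to 7% at an assumed ICC of 0.05 and 7% to 9% at 0.10, the lower end applying if only the intervention arm is clustered. These figures assume equal groups of four and a two-sided test.

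A reader might go on to infer that the trial's p-values will be materially wrong. The documents do not support that, since it would need both an ICC well above the planning value and an analysis that does ignore the groups. The reason to correct the text is that the primary test is affected, its validity should not rest on an unverified planning value, and the correction costs almost nothing.

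**What to change.** State in the analysis section how the weekly randomised group enters each model:

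- **Primary and continuous secondary outcomes:** a linear mixed model with the planned covariates and a random intercept for the weekly group, or ANCOVA with standard errors clustered on the group and a small-sample correction.
- **Binary outcomes:** GEE or mixed logistic regression, clustered on the weekly group.
- **Reporting:** give the observed ICC for the primary outcome, so that the planning value of 0.001 can be judged.

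The cost is analysis wording. No extra data are needed, and about 80 groups are enough for these methods. Confidence intervals become slightly wider if the ICC is above zero and are practically unchanged if it is 0.001.
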